#### Need for further treatment during and following study completion

Treatment to sites other than the selected ‘intrabony site’ throughout the study will consist of subgingival debridement (as allocated by randomisation in test and control patients) and supportive therapy as per protocol. The need for other surgical interventions will be reviewed following the 15 months follow-up. Should deterioration be detected during the study in any sites, where urgent need for surgery or antibiotics is needed, this will be carried out in additional visits during the study and will be documented in the Case Report Forms (CRFs). Following the 15 months follow-up, the possible need for further treatment will be assessed based on residual PPDs > 5 mm [4, 31].

#### Gingival crevicular fluid (GCF) sampling

An ‘intrabony site’ (IS) and a ‘comparison site’ (CS) will be chosen for sampling for each patient among buccal sites. The IS is selected according to the inclusion definitions above. In case of multiple ISs per patient, the site with deepest PPD will be chosen. The CS will be a site with PPD < 4 mm that is not bleeding on probing at the screening visit. Samples of GCF will be collected from the selected IS and CS (for both test and control subjects) at baseline, at the 3 months visit and at the 9 and 15 months follow-ups, prior to periodontal probing to avoid contamination by blood. In the 20 randomly selected subjects taking part in the ‘GTI substudy’, additional GCF sampling will be conducted at day 1 and day 5 visits following initial treatment (for both test and control subjects). Saliva will be removed from the supragingival area using a saliva ejector and cotton rolls, with care taken not to touch the gingival margin area; supragingival plaque, if present, will be removed using a curette to prevent saliva and/or plaque contamination. GCF will be collected for 30 s using methylcellulose strips carefully placed gently at the entrance of the sulcus until slight resistance is felt. GCF volume will be routinely estimated by Periotron (OraFlow Inc., Hewlett, NY, USA). GCF will be immediately extracted in acidic buffer to better preserve inflammatory mediators of periodontal disease from breakdown and/or oxidative processes, which occur to a major extent on the paper strips during storage [32]. GCF samples will then be immediately placed into small conic vials and stored at − 80 °C until time of analysis. Samples will then be processed at the Blizard Institute, Barts and the London School of Medicine and Dentistry, where immunoassay of inflammatory molecules (including, for example, levels of cytokines) and growth factors (for example, bone morphogenetic protein-2 [BMP-2]) in the GCF will be performed. The QMUL Centre for Oral Clinical Research (COCR) and the Blizard’s local standard operating procedures, working practices and risk assessments will be followed to ensure the integrity and viability of all samples to be anonymised, labelled, stored and transferred.

#### Subgingival plaque sampling

Following GCF collection, the IS and CS will have samples of subgingival plaque collected (for both test and control subjects) from the palatal/lingual aspect. Plaque samples will be collected from the selected IS and CS (for both test and control subjects) at baseline, at the 3 months visit and at the 9 and 15months follow-ups. In the 20 randomly selected subjects taking part in the GTI substudy, additional plaque sampling will be conducted at day 1 and day 5 visits following initial treatment (for both test and control subjects). Ahead of the sampling procedure, the supragingival plaque will be carefully removed and the site isolated with cotton rolls and gently dried. A sterile curette will then be inserted to the bottom of the pocket and removed after a single stroke, and the content will be placed in a test tube containing reduced transport fluid until time of analysis. Plaque samples will be analysed using next generation marker DNA sequencing to characterise the subgingival microbiota in order to identify and determine the levels of key periodontal bacterial pathogens and microbial community-wide changes in sites treated with both test and control protocols.

#### Geometric thermal imaging (GTI) substudy

A random sample of 20 subjects (10 in each arm) will be randomly selected to take part in the GTI substudy. The GT image capturing, which is based on the principle of optical triangulation, is non-contact and non-invasive to the patient, and it aims to clarify differences in the wound healing pattern and association to clinical and patient-centred outcomes between the two groups. These subjects will undergo all study visits in the same way as other subjects but will attend the additional imaging analysis at some study visits, as well as at some additional visits as outlined below. The image capture, analysis and measurements will be performed in the selected participants at baseline, day 1 and day 5 after non-surgical treatment and 3 months and 9 months follow-ups, and, in the surgical group, additional measurements will be performed at 1 week and 1 month after surgery.

#### Patient-reported outcomes (PROMS)

A substantial body of evidence suggests that the presence of periodontitis has a considerable effect on the quality of life of affected individuals [33]. This effect will be assessed by measuring patient-reported outcome measures (PROMs). Patient-reported outcomes will be collected using validated patient questionnaires (Oral Impact on Daily Performance (OIDP), EuroQol five-dimension (EQ-5D) scale and global ratings for periodontal health and quality of life [QoL]) [34–36] at baseline and at the 3, 9 and 15 months follow-ups. In addition, subjects allocated to the control group (MIST) will provide PROMS at the 1-week review appointment after the surgical procedure. Furthermore, the subjects allocated to the GTI subgroup will provide PROMS at the 1 day and 5 days post-treatment visits.

#### Statistical analysis plan

The objectives and outcomes are to investigate whether MINST is not inferior to M-MIST in terms of intrabony defect depth healing in patients with periodontitis after 15 months follow-up. These outcomes are measured as:Primary outcome: radiographic intrabony defect depth changeSecondary outcomes:o PPD and CAL change (in millimetres)o Inflammatory markers and growth factors in GCFo Bacterial detection associated with presence of intrabony defectso Gingival inflammation and healing (as measured by GTI in a subset of 10 test and 10 control patients)o PROMs.

The sample size calculation was based on the assumption that the proposed modified MINST protocol is an acceptable alternative to the M-MIST protocol (non-inferiority), with the advantage of reduced costs and morbidity. A non-inferiority margin of 1 mm is considered to be the largest difference that is acceptable between MINST and M-MIST (a lower threshold than the expected difference in bone gain between regenerative surgeries and open flap debridement in intrabony defects) [12] for MINST to be adopted in clinical practices because of the associated advantages of MINST. Single-flap approaches such as M-MIST have previously been reported to lead to radiographic bone gains from 1.8 ± 1.2 mm [37] to 2 mm [38] to 3.5 ± 1.0 mm [14] in small trials. MINST has been reported to lead to 2.4 ± 2.1 mm radiographic bone gain in a retrospective study [17]. Therefore, we assume that the two protocols lead to the same bone gain for the sample size calculation. Accounting for a 10% drop-out rate and using a pooled standard deviation of 1.27, recruiting *n* = 66 participants will be sufficient to confer 90% power to reject the inferiority null hypothesis. Should the true mean bone gain difference between MINST and M-MIST be 0.19 mm in favour of M-MINST, the study would retain a statistical power of 80%. The primary outcome analysis will compare the intrabony defect depth between treatment groups at 15 months using a general linear analysis of covariance (ANCOVA) model with treatment as a factor and the corresponding baseline value as a covariate and adjusting for pre-specified prognostic baseline factors (age, FMPS, BMI, defect angle, tooth mobility). For the primary efficacy endpoint, non-inferiority of M-MIST to MINST could be claimed if the lower limit of the 95% confidence interval (for the difference in mean change of radiographic intrabony defect depth change) is greater than − 1.0 mm. The primary outcome analysis will be the per-protocol analysis; the intention-to-treat analysis will be considered as the sensitivity analysis. For other non-inferiority endpoints the per-protocol analysis will also be considered the main analysis. The superiority endpoint will be analysed on an intention-to-treat basis. Subject-based and site-based analyses will be conducted. The PROM analysis will be based on linear or logistic regression (for continuous/categorical variables) comparing PROM scores or categories of scores at follow-up (3, 9 and 15 months post-intervention) between the two groups, accounting for the respective scores at baseline. We will also look at the minimally important difference for PROMs where applicable, such as in the case of the OIDP, and whether any difference between the two groups is clinically meaningful.

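### The planning SD of 1.27 mm does not fit the SDs quoted beside it for a 1:1 comparison (1.64–1.71 mm), so the stated 90% and 80% power are not supported by the protocol's own inputs

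*Protocol article*

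**What the plan says.** All the inputs stand in one paragraph of the protocol article, under Statistical analysis plan.

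- Surgical arm: single-flap approaches are reported to gain bone "from 1.8 ± 1.2 mm [37] to 2 mm [38] to 3.5 ± 1.0 mm [14] in small trials". Two of the three studies carry an SD.
- Test arm: "MINST has been reported to lead to 2.4 ± 2.1 mm radiographic bone gain in a retrospective study".
- Margin: "A non-inferiority margin of 1 mm is considered to be the largest difference that is acceptable between MINST and M-MIST".
- Main scenario: "we assume that the two protocols lead to the same bone gain for the sample size calculation".
- Variability: the calculation allows for 10% drop-out, "using a pooled standard deviation of 1.27" mm, and concludes that 66 "participants will be sufficient to confer 90% power to reject the inferiority null hypothesis".
- Second scenario, for which the plan gives 80%: "Should the true mean bone gain difference between MINST and M-MIST be 0.19 mm in favour of M-MINST, the study would retain a statistical power". I read the last group name as M-MIST, that is, a deficit for MINST.
- Decision rule: non-inferiority "could be claimed if the lower limit of the 95% confidence interval" lies above −1.0 mm.

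The section on randomisation sets a 2:2:1:1 ratio over the two treatments with and without the thermal imaging substudy. Between treatments this is 1:1.

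**The concern.** In a trial with equal arms, the SD that drives the precision of the treatment difference is the root mean of the two arm variances. The only MINST SD in the paragraph is 2.1 mm, and half the patients will receive MINST. A planning value of 1.27 mm sits close to the surgical SDs and far from what an equal mix would give.

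At stake is the stated power of the trial's single primary non-inferiority claim. If the SD is nearer to what the paragraph quotes, a failure to show non-inferiority could reflect a wide interval and not a worse treatment. A reader who relies on 90% power would be less likely to see it that way.

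**Working it through.** **Inputs.** Margin 1 mm; true difference 0 or 0.19 mm against MINST; SDs of 1.0, 1.2 and 2.1 mm; planning SD 1.27 mm (all from Statistical analysis plan). Recruited 66 with 10% drop-out: 66 × 0.9 = 59.4, taken as 30 and 29 evaluable. No alpha is stated for the sample size. The 95% interval, if two-sided, corresponds to one-sided 2.5%.

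**Method.** Standard error = SD × √(1/30 + 1/29). Power is the probability that a noncentral t variable with 57 degrees of freedom and noncentrality (1 − true difference)/standard error exceeds the critical value (1.672 at one-sided 5%, 2.002 at one-sided 2.5%).

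**Step 1: reproduce the plan's figures with 1.27 mm.** Standard error = 1.27 × √(1/30 + 1/29) = 0.331; noncentrality 1/0.331 = 3.02, or 0.81/0.331 = 2.45 at a 0.19 mm deficit.
- One-sided 5%: 91% and 78%. These match the stated 90% and approximately match the stated 80%.
- One-sided 2.5%: 84% and 67%. These do not match.

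The printed power therefore follows from 1.27 mm at one-sided 5%. The gap between that level and the 95% interval rule is a separate matter; it is kept apart below.

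**Step 2: the equal-arm SD from the quoted values.** SD = √((s₁² + s₂²)/2).
- Surgery 1.0, MINST 2.1: √((1.00 + 4.41)/2) = 1.64 mm.
- Surgery 1.2, MINST 2.1: √((1.44 + 4.41)/2) = 1.71 mm.
- Floor, with zero variance in the surgical arm: 2.1/√2 = 1.48 mm.

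Because of the floor, no value for the SD missing from the 2 mm study can bring the result down to 1.27 mm.

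**Step 3: what 1.27 mm would require.**
- Equal arms with a smaller MINST SD: √(2 × 1.27² − 1.2²) = 1.34 mm to √(2 × 1.27² − 1.0²) = 1.49 mm, in place of 2.1 mm.
- Unequal weights: the MINST variance would carry (1.27² − 1.2²)/(2.1² − 1.2²) = 6% to (1.27² − 1.0²)/(2.1² − 1.0²) = 18% of the weight.
- Covariate adjustment: R² = 1 − 1.27²/1.64² = 0.40 to 1 − 1.27²/1.71² = 0.45 (computed with unrounded SDs).

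**Step 4: power at 66 recruited, no covariate gain.**

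| SD (mm) | One-sided 5%, difference 0 | One-sided 5%, deficit 0.19 | 95% CI rule, difference 0 | 95% CI rule, deficit 0.19 |
|---|---|---|---|---|
| 1.27 | 91% | 78% | 84% | 67% |
| 1.48 (floor) | 82% | 66–67% | 72% | 54% |
| 1.64 | 75% | 59% | 63% | 46% |
| 1.71 | 72% | 56% | 60% | 43% |

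At the level the calculation appears to have used, the SD alone costs 91 − 75 = 16 to 91 − 72 = 19 points. Under the interval rule it costs 84 − 63 = 21 to 84 − 60 = 24 points. The remaining fall, from 91% to 84%, belongs to alpha.

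**Step 5: partial covariate gain, difference 0.** An R² of 0.2 (my assumption) gives a residual SD of 1.47–1.53 mm and power of 80–82% at one-sided 5%, or 69–73% under the interval rule. An R² of 0.3 gives 1.38–1.43 mm and 84–87%, or 75–78%.

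**The case against.** Several points on the other side have weight.

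*The link is inferred.* The text never says that 1.27 mm was pooled from the SDs quoted above it. Those gains lead into the assumption of equal means. Source study sizes are not given, and a pool weighted by them could produce 1.27 mm. This stands as far as it goes: how the value was obtained cannot be known from the article, and asking only for its derivation would be asking for detail that an article may leave out. But weights taken from source studies do not give the variance of a trial that puts half its patients on MINST.

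*The 2.1 mm may not carry over.* It comes from a retrospective study of a slightly different protocol. The Background cites the same source for about 3 mm in non-smokers, which suggests, though it does not prove, that 2.4 ± 2.1 mm describes a wider group; this trial excludes smokers. It also standardises its radiographs and uses one masked, calibrated examiner. These are fair reasons to expect a smaller SD. The paragraph gives none of them as grounds for 1.27 mm, and it uses the same study's mean without reservation.

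*The primary analysis is an ANCOVA.* Adjustment for baseline depth and five prognostic factors will recover some power, so the 60–63% is the no-gain end of a range. This stands. The plan calls 1.27 mm a pooled SD, however, not a residual one, and states no correlation or R².

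*The consequence is limited.* A low planning SD does not bias the estimate or inflate false claims of non-inferiority, and the reported interval will show its own width. This also stands.

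**Conclusion.** The point holds as an inconsistency between the printed planning SD and the printed SDs for a 1:1 comparison: 1.27 mm against a floor of 1.48 mm and a value of 1.64–1.71 mm. The stated 90% and 80% are therefore not supported by the protocol's own inputs. The size depends on two assumptions: that the MINST SD of 2.1 mm applies here, and that covariates explain nothing. On those terms power is about 72–75% at one-sided 5% and 60–63% under the 95% interval rule. At a 0.19 mm deficit it is 56–59% and 43–46%, against the stated 80%.

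A reader might infer more than this, and the documents do not support it:
- That the sum itself is wrong. It is not: with 1.27 mm the figures reproduce at one-sided 5%.
- That the authors gave the MINST variance only 6–18% of the weight. That is merely what a pool of these SDs would need.
- That true power is 60%. This would charge the alpha mismatch to the SD, ignore the ANCOVA, and treat 2.1 mm as settled.

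**What to change.** Keep 66 patients. In the sample size paragraph, replace 1.27 mm with the equal-weight SD from the quoted values (1.64–1.71 mm), or with a residual SD that is explicitly justified and shown with the R² it assumes (about 0.40–0.45 if it is to remain 1.27 mm). If the MINST SD is expected to be below 2.1 mm in this population, say so and give the value used.

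In place of the unconditional 90% and 80%, report power at 66 across SDs of 1.27 to 1.71 mm under the 95% confidence interval rule, for a true difference of 0 and for a 0.19 mm deficit. Without covariate gain this reads 84% down to 60%, and 67% down to 43%.

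The cost is one recalculation, a few lines of text, and a less favourable stated power. No extra patients and no change to the design or the analysis are needed.

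### The stated 90% and 80% power hold for a one-sided 5% test, but the decision rule uses a 95% confidence interval, under which power is about 85% and 68%

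*Protocol article*

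**What the plan says.** Everything needed is in one paragraph of the protocol article, under Statistical analysis plan.

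- Margin: "A non-inferiority margin of 1 mm is considered to be the largest difference that is acceptable between MINST and M-MIST".
- True difference: "we assume that the two protocols lead to the same bone gain for the sample size calculation", that is, zero.
- Variability and loss: "using a pooled standard deviation of 1.27", with 10% drop-out.
- Main power claim: "66 participants will be sufficient to confer 90% power to reject the inferiority null hypothesis".
- Second power claim: with a true difference of 0.19 mm, "the study would retain a statistical power of 80" per cent. The text names the favoured arm as M-MINST. This can only mean M-MIST, because a difference favouring MINST would raise power.
- Decision rule: non-inferiority "could be claimed if the lower limit of the 95% confidence interval" lies above −1.0 mm.

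The paragraph gives no alpha for the sample size. It does not call the interval one-sided, and no 90% interval or one-sided 5% level appears anywhere in the article. The Randomisation section's 2:2:1:1 ratio amounts to 1:1 between the two treatments.

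**The concern.** A sample size for non-inferiority must use the same error level as the rule that decides the trial. A 95% confidence interval without qualification is two-sided, so using its lower limit is a one-sided test at 2.5%. The sample size appears to come from a one-sided test at 5%, which corresponds to a 90% interval. If so, the quoted power belongs to an easier test than the one the trial will apply.

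This is the primary endpoint and the sole basis for the non-inferiority claim. Under the written rule the trial is more likely than stated to miss non-inferiority that is true. The mismatch also leaves open how to call a result whose 90% interval clears −1.0 mm while its 95% interval does not.

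**Working it through.** **Inputs** (all from the Statistical analysis plan section): margin Δ = 1.0 mm; SD σ = 1.27 mm; true deficit δ = 0 or 0.19 mm; drop-out 10%; N = 66, or 33 per arm. Evaluable: 66 × 0.9 = 59.4, so 29 to 30 per arm.

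**Formulas** (normal approximation; non-central t results alongside):

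- n per arm = 2σ²(z₁₋α + z₁₋β)² / (Δ − δ)²
- power = Φ[(Δ − δ)/SE − z₁₋α], with SE = σ√(2/n)

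**Step 1. Reproduce N = 66.** 2σ² = 2 × 1.6129 = 3.2258.

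- One-sided 5%: 3.2258 × (1.645 + 1.282)² = 27.6, so 28 per arm. The t-based calculation gives 29. Then 29/0.9 = 32.2, rounded up to 33 per arm, or **66**. The normal formula alone would give 56/0.9, or 63.
- One-sided 2.5%: 3.2258 × (1.960 + 1.282)² = 33.9, so 34 per arm, or 68/0.9 = 76 recruited. The t-based calculation gives 35 per arm, and 35/0.9 = 38.9, so 39 per arm, or **78** recruited.

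**Step 2. Power with 29 per arm.** SE = 1.27 × √(2/29) = 0.3335. The distance to the margin in SE units is 1/0.3335 = 2.998 when δ = 0, and 0.81/0.3335 = 2.429 when δ = 0.19.

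- One-sided 5%: Φ(2.998 − 1.645) = 91.2% and Φ(2.429 − 1.645) = 78.3%.
- One-sided 2.5%: Φ(2.998 − 1.960) = 85.0% and Φ(2.429 − 1.960) = 68.0%.

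**Step 3. Range over 29 to 30 evaluable per arm.**

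| Test | δ = 0, normal | δ = 0, t | δ = 0.19, normal | δ = 0.19, t |
|---|---|---|---|---|
| Stated | 90% | 90% | 80% | 80% |
| One-sided 5% | 91.2–92.0% | 90.6–91.5% | 78.3–79.5% | 77.5–78.7% |
| One-sided 2.5% (the written rule) | 85.0–86.2% | 83.8–85.1% | 68.0–69.5% | 66.5–68.1% |

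**Step 4. Cross-check on the 0.19 mm.** By the normal formula, the deficit at which power falls to 80% is 1 − (z₁₋α + 0.842) × SE. At one-sided 5% this is 0.17 mm with 29 per arm and 0.18 mm with 30, close to the stated 0.19. At one-sided 2.5% it is 0.07 and 0.08 mm. The second power claim therefore points to the same level as the first.

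**Step 5. Could drop-out have been left out?** The text says it was included. With all 33 per arm evaluable, the 95% rule gives 88 to 89% at no difference but only 72 to 74% at 0.19 mm, so the second claim still fails.

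**The case against.** **The alpha is inferred.** The article states neither level nor sidedness, and the rule uses only the lower limit. If a one-sided 95% bound was meant, 66 patients and both powers roughly agree. This stands as a limit on what can be known, and the fit at one-sided 5% may show what was planned. It does not remove the problem. An unqualified 95% interval is read as two-sided, the text offers no other reading, and the paragraph would need correcting either way. The full protocol is not shown and may state an alpha, but that would not change the conflict between the figures and the rule printed here.

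**The planned analysis is an ANCOVA.** It adjusts for baseline defect depth, age, plaque score, BMI, defect angle and tooth mobility, which could recover power. With 29 to 30 per arm and t-based calculation, 90% at no difference returns if the covariates explain about 15 to 18% of the variance (residual SD about 1.15 to 1.17). Reaching 80% at 0.19 mm needs about 25 to 28%. This is possible, but the article gives no such figure and claims no gain in its calculation. What stands is that 85% and 68% should be labelled unadjusted. In the other direction, the primary analysis is per-protocol, so exclusions beyond 10% would lower power.

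**The reproduction is not exact throughout.** This is fair. N = 66 comes from the t-based calculation with rounding up per arm, and the 80% is matched only to within about 2.5 points.

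**The written rule is the stricter one.** Also true: applied as written, it does not raise the risk of a false non-inferiority claim. The cost falls on power.

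**Conclusion.** The concern holds. On the article's own inputs, the sample size and both powers fit a one-sided 5% test, while the decision rule, conventionally read, is a one-sided 2.5% test. Under that rule, unadjusted power is about 85% (range 84 to 86%) rather than 90% at no difference, and about 68% (range 67 to 70%) rather than 80% at a 0.19 mm deficit. The chance of missing true non-inferiority rises from 10% to about 15%, and from 20% to about 32%.

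This rests on four assumptions: the 95% interval is two-sided; 29 to 30 patients per arm are evaluable; the SD of 1.27 has no reduction from covariates; and the 0.19 mm favours M-MIST.

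**What to change.** In the Statistical analysis plan section:

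1. Keep the two-sided 95% interval as the decision rule and say that it is two-sided.
2. State one-sided alpha 2.5% in the sample size paragraph.
3. Restate power with 66 recruited and 10% drop-out as about 85% at no difference and about 68% at a 0.19 mm deficit in favour of M-MIST, both without covariate adjustment. If a gain from the ANCOVA is to be claimed, give the assumed proportion of variance explained and its source.

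This costs wording only. The stated power becomes less favourable and no patients are added. Restoring 90% at no difference would instead take 78 recruited, 12 more than planned. The interval and its level should be settled before the randomisation code is broken, since the choice between a 90% and a 95% interval could decide a borderline result.

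### The primary non-inferiority rule has the two arms transposed, and the text does not say on which scale or in which order of subtraction the −1.0 mm bound applies

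*Protocol article*

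**What the plan says.** All the quoted text is in the Statistical analysis plan section of the protocol article.

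- **Objective:** "to investigate whether MINST is not inferior to M-MIST in terms of intrabony defect depth healing".
- **Margin:** "A non-inferiority margin of 1 mm is considered to be the largest difference that is acceptable between MINST and M-MIST". The reason given is the adoption of MINST in practice.
- **Sample size scale:** bone gain, where larger is better. "we assume that the two protocols lead to the same bone gain for the sample size calculation".
- **Second power statement:** 80% power is retained if the true difference in bone gain is "0.19 mm in favour of M-MINST". No arm has that label.
- **Primary analysis variable:** "The primary outcome analysis will compare the intrabony defect depth between treatment groups at 15 months", by ANCOVA with the baseline value as a covariate. On this scale larger is worse.
- **Success rule:** "non-inferiority of M-MIST to MINST could be claimed if the lower limit of the 95% confidence interval", where the interval is "for the difference in mean change of radiographic intrabony defect depth change) is greater than − 1.0 mm".

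The Discussion section draws its conclusion in the same direction as the objective: if MINST proves non-inferior to surgery, it may be offered as an alternative.

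**The concern.** The success rule asserts the opposite of what the trial is for. Non-inferiority is one-sided, so exchanging the arms changes which treatment is protected against a false claim. A rule for showing M-MIST non-inferior to MINST puts no limit on how much worse MINST may be.

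The rest of the section does not let a reader repair the sentence with certainty. The margin and sample size are in bone gain, the ANCOVA is on residual depth, and the rule speaks of a change whose sign is not given. Whether a lower limit above −1.0 mm guards against an inferior MINST depends on choices that the text does not make. At stake is the statement on which the primary conclusion of the trial will rest.

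**Working it through.** **Inputs.** Margin 1 mm, SD 1.27 mm, 66 patients, 10% drop-out and 95% interval, all from the Statistical analysis plan section. The split is 1:1 between treatments (2:2:1:1 once the imaging substudy is included), from Randomisation and allocation concealment.

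**1. The plan's own sample size.** Per arm, n = 2·SD²·(z₁₋α + z₁₋β)² / margin².

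- One-sided 0.05: 2 × 1.6129 × (1.645 + 1.282)² = 27.6, so 28. With the t distribution it is 29. Then 29/0.9 = 32.2, so 33 per arm and **66 in total**, as stated.
- One-sided 0.025: 2 × 1.6129 × (1.960 + 1.282)² = 33.9, so 34 (t: 35). After drop-out this is 38 (39) per arm, or 76 (78) in total. This does not give 66.

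**2. The plan's two power figures.** Evaluable patients: 66 × 0.9 = 59.4, or 29.7 per arm. SE = 1.27 × √(2/29.7) = 0.330 mm. Power = Φ((1 − d)/SE − z₁₋α), where d is the true shortfall of MINST in bone gain.

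| | d = 0 | d = 0.19 mm (M-MIST better) |
|---|---|---|
| One-sided 0.05 | 0.918 (t: 0.912) | 0.792 (t: 0.783) |
| One-sided 0.025 | 0.859 (t: 0.847) | 0.691 (t: 0.676) |

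The 90% and 80% are sound at one-sided 0.05, and the 80% needs the 0.19 mm to favour M-MIST. If it favoured MINST, power would be Φ(1.19/0.330 − 1.645) = Φ(1.97) = 0.975. M-MINST is therefore a slip for M-MIST, and the figure itself stands.

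**3. What the bound does under each convention.** With baseline as a covariate, ANCOVA gives the same treatment contrast for 15-month depth and for follow-up minus baseline change. The contrast for depth reduction is the same number with its sign changed. The rule that the lower limit lies above −1.0 then has four possible meanings. The probabilities use a two-sided 95% interval and a MINST that is truly 1 mm worse.

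| Contrast | Expected value | Probability that the rule is met |
|---|---|---|
| Depth reduction, MINST − M-MIST | −1 | Φ((1 − 1)/0.330 − 1.96) = 0.025 |
| 15-month depth, M-MIST − MINST | −1 | 0.025 |
| 15-month depth, MINST − M-MIST | +1 | Φ((1 + 1)/0.330 − 1.96) = Φ(4.1) > 0.999 |
| Depth reduction, M-MIST − MINST (the direction the sentence names) | +1 | > 0.999 |

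**4. Other true differences.**

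| MINST truly worse by | Intended direction | Reversed direction |
|---|---|---|
| 0 mm | 0.86 | 0.86 |
| 0.5 mm | 0.33 | 0.995 |
| 1 mm | 0.025 | > 0.999 |
| 2 mm | about 0 | about 1.00 |

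As an illustration, suppose MINST is observed to leave 1 mm more residual depth. The half-width is 1.96 × 0.330 = 0.65 mm, so the interval for MINST minus M-MIST in depth is about 0.35 to 1.65 mm. Its lower limit is above −1.0, so the literal rule is met. Its upper limit is above +1.0, so non-inferiority of MINST has not been shown.

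**The case against.** The best reply is that two near-identical acronyms were swapped and that the intent is plain. The objective, the margin rationale and the Discussion all ask about MINST. The rule's parenthesis refers to change, the sample size is in bone gain, and on that scale, with MINST minus M-MIST, a lower limit above −1.0 mm is exactly the right bound. Only the arm names would then need swapping. The sign of a change score and the coding of a contrast are also commonly left to the SAP.

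Much of this stands. A reader might infer that a lower limit cannot be right because larger depth is worse, or that the trial would in practice declare a clearly inferior MINST non-inferior. The document supports neither. The mismatch arises only on the depth (or follow-up minus baseline) scale taken as MINST minus M-MIST, or if the sentence is carried out in the direction it names. The silence on scale and order would not by itself be a finding.

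What does not fall away is the rule itself. It is a stated sentence, not an omission, and it contradicts the objective of the same section. The intended arm can be recovered from the context. The scale cannot be recovered with the same confidence, because the section uses two scales with opposite signs.

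**Conclusion.** The point holds: the arms in the primary claim rule are transposed, and this should be corrected because the primary conclusion depends on that rule. The bound of −1.0 mm is not wrong in itself. It is right for MINST minus M-MIST in depth reduction and guards the wrong side under the two literal readings shown. Under those readings a MINST that is truly 1 mm worse passes with probability above 99.9% instead of 2.5%. That figure shows what literal use of the sentence would do; it is not the error rate to expect from this trial. It assumes SD 1.27 mm, 29.7 evaluable patients per arm, a two-sided 95% interval and no precision gained from covariates.

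Two further inferences should be avoided. The M-MINST label does not undermine the 80% figure, which reproduces at one-sided 0.05 when M-MIST is favoured. Nor is this the only confirmatory test that the plan envisages, since the section also mentions other non-inferiority endpoints and a superiority endpoint. It is the only rule written out.

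**What to change.** Replace the rule with wording such as: *Non-inferiority of modified MINST to M-MIST will be claimed if the lower limit of the 95% confidence interval for the ANCOVA-adjusted difference in intrabony defect depth reduction (MINST minus M-MIST) is above −1.0 mm; equivalently, if the upper limit for the adjusted difference in 15-month defect depth (MINST minus M-MIST) is below +1.0 mm.* In the 0.19 mm power sentence, change M-MINST to M-MIST.

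This costs about two sentences, to be settled before the randomisation code is broken. The Trial status section says that protocol amendments go for ethics approval. Correcting the direction leaves N unchanged.

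If the interval is described as two-sided at the same time, restate the power. With 66 recruited and 10% lost it is about 86% at no difference and 69% at 0.19 mm (85% and 68% with the t distribution), not 90% and 80%.
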